## Abstract

**Background:**

Back pain is a major health problem and many sufferers develop persistent symptoms. Detecting relevant subgroups of patients with non-specific low back pain has been highlighted as a priority area for research, as this could enable better secondary prevention through the targeting of prognostic indicators for persistent, disabling symptoms. We plan to conduct a randomised controlled trial to establish whether subgrouping using a novel tool, combined with targeted treatment, is better than best current care at reducing long-term disability from low back pain.

**Methods/Design:**

We will recruit 800 participants aged 18 years and over with non-specific low back pain from 8–10 GP practices within two Primary Care Trusts in Staffordshire, England. Our primary outcome measures are low back pain disability and catastrophising. Secondary outcomes include back pain intensity, global change, leg pain, fear avoidance, anxiety, depression, illness perceptions, patient satisfaction, overall health status and cost-effectiveness. Data will be collected before randomisation, and 4 and 12 months later. Participants are randomised to receive either newly developed interventions, delivered by trained physiotherapists and targeted according to subgroups defined by tool scores, or best current care.

**Discussion:**

This paper presents detail on the rationale, design, methods and operational aspects of the trial.

**Trial registration:**

Current Controlled Trials ISRCTN37113406.

## Background

Back pain is a major health problem in the UK. Each year, approximately 3.5 million people develop back pain [1], and 7–9% of adults consult their GP.[2] Although most sufferers stop consulting their GP within 3 months, 60–80% still have pain or disability a year later.[3,4] Persistent back pain affects peoples' quality of life, their family and social relationships, and impairs their ability to work.[5] Consequently, back pain has a huge economic impact. [6-8]

### Evidence for Treating Low Back Pain in Primary Care

Primary care guidelines for managing low back pain (LBP) [9-11] have been developed within a biopsychosocial framework which recognises that pain is influenced by both tissue pathology and psychological factors, as well as the social context in which the pain occurs. An estimated 85% of LBP consulters will have non-specific LBP, for which diagnostic labelling is discouraged, and treatment depends on the health care providers' preferences and clinical experience.[12] The fundamental question of "who will do best with which treatment" remains unanswered despite a number of high quality primary care-based randomised trials of treatment options for LBP in the last 2 years. [13-18]

### Subgrouping and Targeted Treatment for Low Back Pain

Findings from primary care studies contrast with specialist settings, where there is randomised controlled trial evidence that cognitive behavioural approaches help selected groups of patients with chronic back pain. [19,20] The problem, therefore might be that treatments are not reaching appropriate patient groups, and their effect is diluted by the inclusion of heterogeneous patient populations. Researchers are now questioning the appropriateness of considering non-specific back pain patients to be a homogenous group [21,22], and ways of identifying subgroups of patients who might benefit from specific therapies has been recommended.[23] There is growing evidence that psychosocial factors are particularly useful for predicting individuals who will develop chronic back pain, but in primary care these are difficult to spot and often go unrecognised.[17,24] Even when primary care clinicians do recognise psychosocial influences, they may be unable to manage them effectively (without additional training).[25] Researchers in some settings have developed clinical prediction rules to identify patients who are more likely to respond to specific treatments.[26,27] Other groups have developed and validated screening tools that identify patients at risk of work absence.[21,28] Early indications show these approaches to be promising, with improved outcomes when subgrouping is used to guide treatment decision-making.[29] Although it is recognised that these types of studies may improve the management of back pain patients, the implementation of such systems remains unclear, and research on the identification and treatment of subgroups of patients is highlighted as the "main challenge" for the treatment of LBP.[23]

### Development of the Subgrouping Tool

In response to this challenge, a simple-to-use LBP subgrouping tool for use in primary care – the STarT Back Tool – has been developed. [30-32] This tool classifies patients into 3 categories for targeted treatment, based on the presence of potentially modifiable physical and psychological prognostic indicators for persistent, disabling symptoms, identified through 9 questions. Patients are classified as "low risk" of future disabling LBP if they score positively on fewer than 4 questions. The remainder are then subdivided into "medium risk" (physical and psychosocial indicators for poor outcome, but without high levels of psychological indicators) and "high risk" (high levels of psychological prognostic indicators with or without physical indicators).

### Development of the Targeted Treatment Interventions

Alongside the development of the STarT Back tool, we have developed targeted treatments for patients allocated to the low, medium and high-risk subgroups; these have been designed to address the specific modifiable prognostic indicators identified by the tool. Evidence-based assessment and treatment approaches for LBP patients have been agreed and follow a "stepped-care" format. The focus of the interventions is directed towards the secondary prevention of disabling back pain. A three-month pilot study completed in September 2006 demonstrated that the study methods were feasible and acceptable in a LBP primary care population consulting their GP and seeking treatment. They also showed that it is feasible to recruit and treat the numbers of patients required for the trial within the set timeframe.

### Trial Objectives

The primary objective of this Trial is to compare the overall effectiveness of a "subgrouping for targeted treatment" approach with "best current care" (non-targeted) physiotherapy practice, over a 12 month period, for LBP. The targeted treatments are delivered by specially trained community physiotherapists.

Secondary objectives are: a) to investigate the change in prognostic indicators separately for each subgroup (high, medium and low risk) in the "targeted treatment" arm compared with the change in the corresponding subgroup in controls receiving "best current care" (non-targeted) physiotherapy practice; and b) To evaluate the cost effectiveness of the new model of care compared with "best current care".

## Methods

### Setting

Participants will be recruited from 8–10 general practices within the Keele GP Research Partnership. This Partnership includes a network of 30 practices that are committed to high quality consultation recording using Read Codes.[33] The population in this locality is primarily urban with some rural and inner city areas, and is therefore broadly representative of the population in the UK. Community Back Pain Clinics, through which patients can be recruited to the Trial, are held at two Primary Care Centres within this locality.

### Ethical approval

Ethical approval was obtained from the North Staffordshire Local Research Ethics Committee in February 2007 (ref number 07/Q2604/5).

### Eligibility criteria

Male and female subjects aged 18 years and above who seek care for LBP with or without associated leg pain are eligible to take part. Participants must speak and understand English and be willing and able to give full, informed written consent. The exclusion criteria are: potentially serious pathology (e.g. cauda equina compression, inflammatory arthritis, malignancy etc), serious co-morbidity, psychiatric illness or personality disorder; spinal surgery in the last 6 months; pregnancy; already receiving treatment other than GP care for this episode of back pain; and inability to attend regular physiotherapy appointments.

### Recruitment

Participants are identified when they consult their GP, practice nurse or the local Physiotherapy Direct Access service (Physio Direct) for LBP. At the GP practices, previously validated back pain Read Codes will be used to identify patients.[2] When a clinician enters one of these Read Codes, a pop up screen will remind them that the patient will be invited to a Community Back Pain Clinic. At this point the clinician can choose to "opt out" if the patient is considered to be inappropriate for referral to the Clinic, and/or is ineligible to take part in the Trial. The remaining patients are given an information sheet about the Clinic. One participating GP practice uses the local "Physio Direct" service, which offers direct access for patients with back pain, without the need for an initial consultation with their GP. Patients from this GP Practice who telephone the Physio Direct service instead of consulting their GP are initially assessed over the phone by a physiotherapist. Potentially eligible patients will be told about the Community Back Pain Clinic by the assessing physiotherapist and sent a clinic information sheet. All patients identified from the GP practices and Physio Direct are mailed a letter inviting them to telephone for an appointment at the Community Back Pain Clinic, along with a patient information leaflet about the Trial and a baseline questionnaire. Patients who telephone are given an appointment at one of the Community Back Pain Clinics. At the clinic, patients see a research nurse who explains the Trial in detail. For those patients interested in taking part, the nurse then goes through the written informed consent process. The research nurse is blinded to the patient's treatment allocation throughout the trial. All patients are assessed by an experienced physiotherapist at the clinic, regardless of whether they choose to take part in the Trial or not.

### Baseline assessment

All patients invited to the Community Back Pain Clinic are requested to complete the postal questionnaire and those who consent to take part in the study complete a further self report questionnaire in clinic. The questionnaires include the STarT Back Tool [32], age, gender, educational attainment and the outcome measures listed in Table 2 at time point zero.

### Treatment allocation

Following completion of the baseline questionnaire, patients who consent to take part in the Trial are randomly allocated to one of the two treatment arms: "targeted treatment" or "best current care" (see Figure 1). After calculating the patient's STarT Back tool score from the postal questionnaire, the clinic administrator telephones the Primary Care Musculoskeletal Research Centre randomisation service.[15,34] Patients are randomised using a stratified block randomisation method according to Centre and risk subgroup. Random allocation is on a 2:1 (targeted treatment: best current care) ratio basis with a block size of three. This gives three possible permutations of treatment allocation per block: AAB; ABA; BAA. The research nurse in clinic is blinded to a patient's treatment allocation.

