## Conclusion

The STarT Back Trial will investigate the clinical and cost effectiveness of a novel subgrouping and targeted treatment approach for patients with non-specific low back pain in Primary Care. Using the results of the Pilot study, we estimate that we can recruit 800 patients to the trial in 12–18 months if we involve 8–10 GP practices from the Keele GP Research Partnership and Physio Direct and run 3 Community Back Pain Clinics a week. Trial recruitment commenced in July 2007 and is currently on target to close before January 2009. Follow up is targeted for completion by February 2010 and results should be finalised for publication in summer 2010.

The primary objective of the trial is to compare the clinical outcomes of subgrouping and targeted treatment with best current care over a 12 month period. The secondary objectives are to compare the clinical outcomes for each of the three subgroups compared with best current care over 12 months; and to evaluate the cost effectiveness of subgrouping and targeted treatment compared with best current care at 12 months.

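### A single fixed block of three at 2:1 leaves 44% of allocations deducible by anyone holding the stratum's history: a minor residual risk to concealment, mainly through the clinic administrator

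*Protocol article*

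**What the plan says.** The Treatment allocation section sets the strata: "Patients are randomised using a stratified block randomisation method according to Centre and risk subgroup". It then fixes the block: "Random allocation is on a 2:1 (targeted treatment: best current care) ratio basis with a block size of three". It also lists every possible block: "This gives three possible permutations of treatment allocation per block: AAB; ABA; BAA". No varying or undisclosed block size is mentioned.

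On who does what, the same section says: "After calculating the patient's STarT Back tool score from the postal questionnaire, the clinic administrator telephones the Primary Care Musculoskeletal Research Centre randomisation service". It adds: "The research nurse in clinic is blinded to a patient's treatment allocation". Allocation follows consent and the baseline questionnaire.

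Under Interventions, targeted-arm physiotherapists use the tool score and deliver a defined package. The control consultation is given by a different physiotherapist who does not see the tool result.

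The Setting section says the clinics "are held at two Primary Care Centres within this locality". The Conclusion says recruitment began in July 2007 and "is currently on target to close before January 2009", so the block size is published while recruitment is under way.

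**The concern.** A block of three at 2:1 holds one control allocation. Once it has appeared, the rest of the block must be targeted treatment; after two targeted allocations, the next must be control. A telephone service hides the list, but it cannot hide an allocation that follows from those already issued.

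To make the deduction, a person needs both the stratum and the run of past allocations in it. The clinic administrator calculates the score, which gives the risk subgroup, and makes each randomisation call. Care differs visibly by arm, so allocations do not stay hidden after they are made.

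What is at stake is selection. If the expected arm influenced when a patient was booked, or reached the nurse before the consent discussion, the arms could differ at entry in ways that baseline scores do not capture.

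**Working it through.** **Inputs** (protocol article): ratio 2:1, one block size of 3, blocks AAB, ABA and BAA (Treatment allocation); 800 patients, about 533 and 267 per arm (Sample size); two clinic sites (Setting); three risk subgroups. Assumptions: the three blocks are equally likely, and "Centre" in the stratification means clinic site, which gives 2 × 3 = 6 strata.

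**The plan's own figures.** Permutations: 3!/(2! × 1!) = 3, as stated. Arms: 800 × 2/3 = 533 and 800 × 1/3 = 267, as stated.

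**Certain allocations under the stated design**, for someone who knows the stratum's history:

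- Position 1: never certain, probability 0.
- Position 2: certain only after a first B, probability 1/3.
- Position 3: always certain, probability 1.
- Mean: (0 + 1/3 + 1)/3 = 4/9 = 44.4%. Over 800 patients, 800 × 4/9 ≈ 356.

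By arm, across the nine positions of the three blocks, 3 of 6 targeted allocations (50%) and 1 of 3 control allocations (33%) are certain. Unfinished last blocks lower these figures slightly.

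**Best-guess accuracy under the stated design:**

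- Position 1: 2/3.
- Position 2: (2/3 × 1/2) + (1/3 × 1) = 2/3.
- Position 3: 1.
- Mean: (2/3 + 2/3 + 1)/3 = 7/9 = 77.8%. Always naming targeted treatment scores 66.7%.

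**Alternatives at the same 2:1 ratio.** Fixed blocks come from exact enumeration. Mixed blocks come from simulated sequences of 133 allocations (800/6), with an observer who knows the set of sizes but not where blocks begin.

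| Design | Certain allocations |
|---|---|
| Fixed 3 (as planned) | 44.4% |
| Fixed 6 | 13/45 = 28.9% |
| Fixed 9 | 3/14 = 21.4% |
| Random mix of 3 and 6 | about 10% |
| Random mix of 3, 6 and 9 | about 4% |

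Under the 3, 6 and 9 mix, best-guess accuracy is about 74%. A larger fixed block helps less than varying the size. The 25/50/25 risk split would make strata about 100, 200 and 100 per centre rather than 133 each (if the two centres are equal); rerunning at 100 and 200 leaves the rounded figures for the mixes unchanged.

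**Can the sequence be followed?** The Conclusion plans 800 patients in 12–18 months at three clinics a week. That is 800/(52 × 3) ≈ 5.1 to 800/(78 × 3) ≈ 3.4 randomisations per clinic, spread over up to six strata. One person making the calls could keep track of that.

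**The case against.** The document closes most routes from prediction to biased entry.

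- **Clinician opt-out.** A reader might infer that eligibility opt-outs could be steered by the expected arm. Under Recruitment, the opt-out happens at the consultation, before the invitation, questionnaire and tool score. Nothing gives that clinician the stratum or the sequence.
- **Consent.** The research nurse explains the trial and takes consent, and is blinded to allocation throughout. Randomisation follows consent.
- **Physiotherapists.** A reader might infer that they can predict because they know which arm they treat. Control physiotherapists are blinded to the tool score. Targeted-arm physiotherapists are not described as seeing control allocations. Neither group is given a role in enrolment.
- **Inseparable bias.** A reader might infer that any selection bias could not be told apart from the treatment effect. Stratification by risk subgroup and adjustment for baseline scores limit it on the main prognostic variables. Self-reported outcomes in an unblinded trial raise response bias, which is a different matter.
- **Size of the gain.** Best-guess accuracy falls by only about 4 points (78% to 74%), and late in recruitment the change reaches fewer patients.

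All of this stands and lowers the severity. What remains is the administrator. The score comes from a questionnaire posted with the clinic invitation, so the stratum could be known before the consent discussion. The article does not say when the questionnaire is returned or scored, nor who books appointments. Allocation after consent therefore does not by itself rule out influence through booking or an expectation passed to the nurse. Baseline adjustment does not reach unmeasured prognosis.

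**Conclusion.** The point holds as a minor residual risk to allocation concealment. The stated design makes 4/9 (44%) of allocations certain, with 78% best-guess accuracy, to anyone with the full history of the stratum. That figure is exact for complete, equally likely blocks. On the text it applies mainly to the clinic administrator.

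The step from predictability to bias is conditional: the administrator would have to influence booking or pass an expectation to the nurse. The document describes neither, so it gives no ground for saying that allocation was subverted or that the treatment estimate is biased. The block size is stated outright in the article, so this is not a detail left to an unseen analysis plan.

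**What to change.** For all remaining randomisations, have the existing central service generate new lists within each Centre by risk-subgroup stratum, with block sizes varying at random (for example 3, 6 and 9) and the 2:1 ratio kept. Do not disclose the new sizes to clinic staff. In the trial report, state who had access to previous allocations while the fixed block of three was in use.

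The cost is new lists and slightly more possible imbalance from unfinished blocks. In an unfinished block of three, the control count can differ from one third of those allocated by at most 2/3 of a patient (after AA: 0 against 2/3). In a block of nine it can differ by at most 2 (after six A: 0 against 2). Over six strata the extreme is 6 × 2 = 12 patients, against about 267 controls. The benefit is limited to patients not yet randomised.

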**Figure 1 F1:**
[figure not shown]
STarT Back Trial Flow Chart.

### Interventions

#### 1) Targeted Treatment

All patients randomised to 'targeted treatment' receive an initial 30-minute protocolised intervention with a specially trained study physiotherapist. Patients receive reassurance about the benign nature of their pain, and simple messages of advice around issues such as pain relief, appropriate activity levels and the role of further investigations. The physiotherapist is guided by the results of the patient's STarT Back tool score so that specific concerns can be identified and addressed on an individual basis. To reinforce key messages the 'Back Book' [35] is given, together with an information sheet of local contacts for exercise venues such as swimming pools, gyms and exercise on prescription, and self-help groups. A 15-minute educational video based on The Back Book, called 'Get Back Active' [36] is shown to patients to reinforce key messages. Patients allocated to the 'low risk' group receive no further treatment in addition to this 30 minute clinic appointment.

For patients allocated to receive the medium and high risk subgroup interventions, the study administrator arranges further appointments with specially trained physiotherapists within two weeks of their clinic date. Treatments for the medium and high risk groups were developed after reviewing available literature and guidelines to identify best practice treatment, and are delivered during a target time of six weeks. The focus was to provide secondary prevention of disabling back pain through the provision of treatment targeted at the specific modifiable prognostic indicators identified by the STarT Back tool (see below).

Patients in the 'medium risk' group present with predominantly physical prognostic indicators (disabling back pain, referred leg pain and co-morbid pain), without high levels of psychosocial distress. The 'medium risk' group package of care therefore, targets physical characteristics using a range of physiotherapy techniques delivered over 6, 30-minute sessions. Management includes an assessment and differential diagnosis (particularly for patients with referred leg pain), and treatment designed to reduce disability related to future episodes of low back pain.

The 'high risk' group physiotherapy treatment is tailored for patients who present with high psychosocial indicators such as anxiety and fear. Therapists are given extra training to deliver this package, which helps them identify and address pain related psychological distress through the use of appropriate cognitive behavioural strategies. Goal setting, where realistic treatment goals are negotiated with patients using a Goal Attainment Scale.[37] The components of the targeted treatments are outlined in Table 1.

**Table 1 T1:** Components of Targeted Treatment

**Low, medium and high risk groups **(30-minute structured intervention)
• Evidence-based assessment of LBP presentations, according to current guidelines.
• Advice on back care emphasising positive messages about activity, pain relief and work.
• Patients are given a copy of "The Back Book" [35] and see a 15-minute video based on The Back Book entitled "Get Back Active" [36].

**Medium and high risk groups**
• Treatment according to STarT Back assessment and treatment algorithms and STarT Back physiotherapy manual.
• Evidence-based physiotherapy techniques addressing 'signs and symptoms' in non-specific LBP presentations, according to current recommendations from guidelines and high quality clinical trials.
• Evidence-based advice, education and reassurance for symptoms and management, according to guidelines and current literature within the biopsychosocial model.

